**Methods:**

We will enroll 352 rural older (aged >50 y) people living with HIV and test the interventions using a 2 (social support groups: yes or no) × 2 (strengths-based case management: yes or no) factorial design. Supportive-expressive peer social support groups aim to increase social support and lower HIV stigma, thereby improving HIV health outcomes and quality of life. Trained facilitators will deliver the 8 weekly sessions with a set curriculum to groups of 8 to 12 participants via videoconference. Strengths-based case management is an individual-level, individually tailored intervention delivered by trained staff. Over 5 sessions, the participant-staff duo selects a barrier impacting HIV care or quality of life and identifies short-term goals to overcome the barrier, focusing on the process of incremental problem-solving while recognizing accomplishments. We will assess HIV viral load—using participant-collected dried blood spot samples—at baseline and 8 and 12 months after the intervention. Using surveys, we will assess adherence, quality of life, depressive symptoms, and secondary outcomes at baseline and 4, 8, and 12 months after the intervention. We hypothesize that participants randomly assigned to each intervention will be more likely to be virally suppressed and adherent to antiretroviral therapy and have higher quality of life and fewer depressive symptoms at follow-up than those not assigned to each intervention. Secondary hypotheses are that, compared to those not receiving each intervention, participants in each intervention will report greater social support, self-efficacy, and likelihood of accessing needed services; less loneliness and internalized HIV stigma; and fewer structural barriers. Data will be analyzed using generalized linear mixed models.

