### Supportive-Expressive Peer Social Support Group Intervention

Supportive-expressive peer social support groups are an evidence-based intervention with the objectives of increasing social support, reducing loneliness, and reducing internalized HIV stigma and in turn improving antiretroviral therapy (ART) adherence, viral suppression, depressive symptoms, and quality of life.

Social isolation is a prominent issue faced by many older people living with HIV, particularly those living in rural areas [12]. Low levels of perceived social support have been shown to negatively impact adherence to medication among older people living with HIV [22], and increasing social support can lead to improved health outcomes and reduced internalized HIV-related stigma [23]. A review of support groups for people living with HIV found that support group interventions were associated with reductions in morbidity and mortality and improvements in retention in care and quality of life [24]. However, the benefits of in-person support groups may be unavailable to rural-dwelling older people living with HIV due to their geographic isolation. Older rural people living with HIV may be unable to access these groups due to limited transportation options, long travel distances, and limited group availability in their areas.

On this evidence base, we lightly adapted the supportive-expressive peer group therapy intervention from Project Linkage [25] for remote delivery to older rural people living with HIV. When delivered by telephone, this intervention was shown to reduce depressive symptoms among older people living with HIV [25]. However, its efficacy for improving viral suppression, medication adherence, and quality of life for older people living with HIV has not been tested, nor has it been delivered by videoconference.

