### Measures

Primary and secondary outcome measures along with covariates are described in Table 1. Primary outcomes include DBS-assessed viral suppression, ART adherence, health-related quality of life, and depressive symptoms. The secondary outcomes are potential mediators of intervention effects, including social support, loneliness, internalized HIV stigma, general self-efficacy, treatment adherence self-efficacy, social and medical service use, and structural barriers (such as transportation as a barrier to care and housing instability). All primary and secondary outcomes are assessed in each survey (at baseline and 4, 8, and 12 mo) except for viral suppression, which is assessed via DBS at baseline and 4 and 12 months. Covariates are variables that will be controlled for in outcome analyses should they differ across randomized conditions or be associated with retention. We also include measures of feasibility and acceptability in the 4-month survey.

**Table 1 table1:** Study measures.

Domains and subdomains			Description or scale

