**Secondary outcomes (baseline and 4, 8, and 12 mo)**			
	Social support	Scale score (1-5) on the MOS^e^ social support survey [43]	
	Loneliness	Scale score (1-5) on the loneliness survey from the NIH^f^ Toolbox [44]	
	Internalized HIV stigma	Scale score (1-5) on the internalized stigma subscale of the HIV Stigma Mechanisms Scale [45]	
	General self-efficacy	Scale score (1-5) on the New General Self-Efficacy Scale [46]	
	Treatment adherence self-efficacy	Scale score (0-4) on the HIV-ASES^g^ [47]	
	Service use	Participants will report which of 12 HIV-related social and medical services they have needed during the previous 3 mo and which of these needed services they were able to obtain [48]; a composite variable will indicate whether participants successfully accessed at least 1 needed service (0=no, 1=yes)	
	Structural barriers	Participants will report barriers faced in the past 3 mo, with items assessing the following: not having current health insurance, transportation as a barrier to health care, finances as a barrier to health care, not having enough food to eat, not having stable housing, and lacking eHealth literacy; the number of barriers will be summed (scores 0-6)	

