Finally, analyses will explore the mediators of intervention effects on outcomes to shed light on the potential mechanisms of intervention effects. Understanding mediating mechanisms can help guide future efforts to optimize programs by capitalizing on the key processes involved in generating health outcomes. Mediation will be tested in a structural equation model, which will be fit in Mplus (Muthén & Muthén) [57] using a full-information maximum likelihood estimator robust to nonnormality. The model will include effect-coded interventions as predictors; social support, loneliness, self-efficacy, service use, and structural barriers as mediators; and viral suppression, adherence, quality of life, and depressive symptoms as outcomes. For a longitudinal test of mediation, models will include mediators assessed at 4 months and outcomes assessed at 8 and 12 months. Paths will lead from interventions to all mediators and from all mediators to all outcomes. Residual correlations between different mediators and different outcomes will be allowed, and covariates will be included as needed. Although we anticipate specific mechanisms for each intervention, this method will allow for a complete understanding of the mechanisms. We will use bootstrapped CIs to assess the indirect effects of the interventions on outcomes via mediators.

To inform future intervention implementation, we will also summarize information related to the acceptability and feasibility of each intervention and of the HemaSpot DBS testing for viral load. Acceptability will be assessed by survey items (Table 1). In terms of feasibility, we will summarize participation in each intervention (eg, number of sessions attended).

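### The exploratory mediation model leaves out internalized HIV stigma, a named mechanism of the support groups, so that pathway cannot be tested and its effect can be credited to other mediators

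*Protocol article*

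**What the plan says.** All places are in the protocol article.

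- **Mechanism, abstract (Methods).** The support groups "aim to increase social support and lower HIV stigma, thereby improving HIV health outcomes and quality of life".
- **Mechanism, introduction (section on the support group intervention).** The objectives are "increasing social support, reducing loneliness, and reducing internalized HIV stigma", and these are said to lead in turn to better adherence, viral suppression, depressive symptoms and quality of life.
- **Measures.** "The secondary outcomes are potential mediators of intervention effects, including social support, loneliness, internalized HIV stigma", followed by the self-efficacy scales, service use and structural barriers.
- **Table 1, secondary outcomes (baseline, 4, 8 and 12 months).** "Scale score (1-5) on the internalized stigma subscale of the HIV Stigma Mechanisms Scale".
- **Statistical Analysis, mediation paragraph.** The two interventions, effect coded, are the predictors, with "social support, loneliness, self-efficacy, service use, and structural barriers as mediators". All four primary outcomes, viral suppression among them, are the model's endpoints. Mediators are taken at 4 months and outcomes at 8 and 12 months. On structure: "Paths will lead from interventions to all mediators and from all mediators to all outcomes". The paragraph says that this will give a complete picture of the mechanisms.

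**The concern.** The article defines its potential mediators once, in Measures, and then lists the mediators of the model in Statistical Analysis. The second list drops one construct without giving a reason, and it is one of the three mechanisms claimed for the support groups. The group curriculum was revised after the pilot specifically to bring in HIV-related stigma.

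Two consequences follow. First, the route from support groups through lower stigma to the outcomes gets no estimate. Second, the remaining estimates can be distorted. If stigma and perceived support are correlated and stigma affects the outcome, a model without stigma attributes part of its effect to support or loneliness. Allowing residual correlations among the included mediators does not cure this, because stigma is not one of them. The stated purpose of the analysis is to guide later optimization of the programs, and a misattributed mechanism would misdirect that work.

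The same paragraph asks for viral suppression at 8 and 12 months, while the Methods schedule has no 8-month viral load.

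**Working it through.** The documents give no figure for this point, so the check compares lists and schedules. An illustration on assumed inputs then shows the size.

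**1. Mediator lists**

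| Construct in Measures | In the mediation model? |
|---|---|
| Social support | yes |
| Loneliness | yes |
| Internalized HIV stigma | **no** |
| Self-efficacy (general; treatment adherence) | yes, if the single term covers both scales |
| Service use | yes |
| Structural barriers | yes |

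Stigma is the only construct missing. The paragraph on secondary outcomes, also in Statistical Analysis, does include it.

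**2. Outcome timing**

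The model has 4 outcomes × 2 visits (8 and 12 months) = 8 outcome-by-visit cells. Overview of Study Design, Procedures, Measures, Table 1, HIV Viral Load Testing and Statistical Analysis all place viral load at 4 and 12 months (with baseline where that is stated). So 7 cells have data and 8-month viral suppression has none. The abstract alone gives baseline, 8 and 12 months.

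**3. Size of the misattribution (illustration)**

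Assumed, not from the documents: a continuous outcome with higher values better; assignment X coded 0/1 in equal numbers (variance 0.25); effect on support a = 0.35 and on stigma -0.35, in residual SDs; residual correlation r = -0.4 between support and stigma; stigma-to-outcome path c = -0.3; no effect of support and no direct effect.

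Without stigma and without a direct path, the support-to-outcome slope is

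|c| × (|r| + a² × 0.25) / (1 + a² × 0.25)
= 0.3 × (0.4 + 0.030625) / 1.030625 = 0.125.

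False indirect effect = 0.35 × 0.125 = **0.044 SD** between those assigned and not assigned. The true effect through stigma is 0.35 × 0.3 = 0.105, so about 42% of it (0.044 / 0.105) is credited to support.

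With a direct path but still no stigma, the slope is |c| × |r| = 0.12, and the indirect effect is 0.35 × 0.12 = 0.042. With stigma in the model, the expected slope is 0.

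A simulation of this set-up (200 replicates, n = 282, which is 352 × 0.80) agrees: mean slopes 0.127, 0.122 and 0.004, and indirect effects 0.044, 0.043 and 0.001. Nearly all of the distortion comes from leaving out stigma and very little from the direct path.

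**4. Range**

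Same formula, no stigma and no direct path:

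| r | c | Slope | False indirect effect |
|---|---|---|---|
| -0.4 | -0.3 | 0.125 | 0.044 |
| -0.2 | -0.3 | 0.3 × 0.230625 / 1.030625 = 0.067 | 0.023 |
| 0 | -0.3 | 0.3 × 0.030625 / 1.030625 = 0.009 | 0.003 |
| -0.4 | -0.1 | 0.1 × 0.430625 / 1.030625 = 0.042 | 0.015 |
| -0.4 | 0 | 0 | 0 |

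**5. If support does have an effect**

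In a second simulation the support-to-outcome path is 0.3 and the other inputs are as in step 3. With -1/+1 coding, a true indirect effect of 0.175 × 0.3 = 0.0525 per coded unit is estimated as about 0.074 without stigma and 0.052 with it. That is an overstatement of about 40%.

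**The case against.** **The analysis is exploratory and most of it is sound.** This stands. A reader might infer that the model cannot test the stated mechanisms at all. The article does not support that: all four pathways proposed for case management, and two of the three for the support groups, are in the model. The effect of each intervention on stigma is also still tested as a secondary outcome, so whether the groups lower stigma will be known. What goes untested is whether lower stigma carries an effect through to the outcomes.

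**The path description is condensed.** A reader might infer that direct intervention-to-outcome paths are excluded and full mediation is imposed. The text names no direct path, but it does not set one to zero either, and the working shows that this choice moves the illustrated slope only from 0.127 to 0.122. It is a matter for clarification.

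**Baseline mediator and outcome values are not listed as covariates.** The article says covariates enter as needed. Which ones is detail that an article commonly leaves to the analysis plan, so this is no fault here.

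**The 8-month viral suppression wording is loose but harmless.** In part this stands. The Methods are clear elsewhere, and a variable with no data cannot be fitted by mistake. The sentence still asks for something that will not exist, and the abstract gives a different schedule, so the wording needs correcting.

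**The illustration is built to show bias.** It is: all its inputs are assumed, and giving support no effect of its own makes the false mechanism look starkest. For that reason a range is shown. The omission itself needs no illustration, because it is visible from the lists.

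**Conclusion.** The point holds for the omission of internalized HIV stigma. The mediator list contradicts the article's own account of how the support groups work and its own definition of potential mediators. The claim to a complete picture of the mechanisms is therefore not met.

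The size of any misattribution is unknown. On the assumed inputs, a false indirect effect of about 0.04 SD is credited to social support. It falls to about 0.02 at a residual correlation of -0.2 and to nearly 0 when the correlation or the stigma path vanishes. These figures assume a linear model with a continuous outcome and carry over only in direction to viral suppression and adherence.

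The 8-month viral suppression wording is a smaller error of the same paragraph, and the direct paths need only a clarifying statement. The primary efficacy tests are not affected.

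**What to change.** 1. Add internalized HIV stigma at 4 months to the mediators, with the same paths as the others.
2. In the same paragraph, take viral suppression at 12 months only and keep the other three outcomes at 8 and 12 months. Reconcile the abstract's 8- and 12-month viral load schedule with the Methods.
3. State that direct paths from both interventions to the outcomes are included.

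**Cost.** The stigma data are already in every survey, so only the model specification changes, and it can be changed before analysis. If each outcome visit enters separately, stigma adds 2 paths from the interventions and 7 paths to the outcomes, plus its residual correlations with the other mediators. Expect somewhat wider intervals for the indirect effects, since correlated mediators will share information. No change to data collection, randomization or the primary analysis is needed.

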## Results

Recruitment and enrollment began in April 2024, with 177 participants consented as of July 2025. Recruitment is planned to conclude by April 2026. Final participant follow-ups will end by April 2027, followed by data analysis. RCT results will be disseminated by 2028 via peer-reviewed publications, presentations at scientific meetings, and ClinicalTrials.gov. Results will also be disseminated to AIDS service organizations and other community organizations via a written report and webinars. If the interventions are shown to be efficacious, full manuals will be made available to the public on our website.

## Discussion

### Contributions to the Field

This manuscript describes the protocol for an RCT testing the efficacy of 2 remotely delivered interventions that aim to improve viral suppression, medication adherence, health-related quality of life, and depressive symptoms among rural older people living with HIV in the southern United States. These interventions are designed to reach and engage rural older people living with HIV, a growing yet underserved population in need of health-related services. Innovations of this research include the focus on rural older people living with HIV; remote delivery of interventions to participants at home, overcoming transportation and distance barriers often faced by rural older people living with HIV; and objective assessment of viral suppression via self-collected DBS specimens.

### Limitations

Our study protocol has several limitations. First, although our multiple recruitment methods are designed to reach people living with HIV with varying levels of care engagement, including those with low engagement in care who are not virally suppressed, our partial reliance on AIDS service organizations for recruitment may lead to underrepresentation of those with the lowest care engagement. However, we have reached participants with suboptimal engagement in care and medication adherence and detectable viral loads in our previous studies with this population [18,19,21]. Similarly, because there may be lower barriers to screening online (vs placing a call to study staff) and because some recruitment activities will take place online, we may be more likely to reach participants who use the internet. To avoid excluding participants without internet access, we have ensured that there are offline pathways to recruitment (study flyers mailed to potential participants and displayed in community agencies), enrollment (via telephone), survey completion (on paper via mail), and intervention participation (via telephone). Finally, although our study uses an objective measure of viral suppression that has been successfully used in our pilot work, other outcome measures are self-reported.

### Conclusions

If successful, these manualized interventions, delivered to older rural people living with HIV at home, can be scaled up for rural settings across the United States, improving health equity. We hope that the results from this study will provide us with tools to improve health outcomes for a vastly understudied population and therefore advance the US “Ending the HIV Epidemic” initiative.

## Appendix

Multimedia Appendix 1 Peer review report by PPAH - Population and Public Health Approaches to HIV/AIDS Study Section, Healthcare Delivery and Methodologies Integrated Review Group (National Institutes of Health, USA).

## Abbreviations

ART: antiretroviral therapy
DBS: dried blood spot
GLMM: generalized linear mixed model
LOD: limit of detection
RCT: randomized controlled trial
REDCap: Research Electronic Data Capture
SBCM: strengths-based case management
